### 3. Sample Size, Selection and Withdrawal of Subjects

A convenience sample of 60 women with current GDM, 30 in each arm will be recruited. King’s College Hospital antenatal diabetes clinic sees around 200 new patients with GDM a year, equating to 17 a month, and Guy’s and St Thomas’ Hospitals see 700 (58 a month). Participants will be recruited opportunistically at their routine clinic appointment upon diagnosis of GDM, group education session the following week, or at a following clinic visit, by a diabetes nurse, consultant or dietician. We estimate that with a 30% recruitment rate we can recruit our sample within 3 months, or with a 15% recruitment rate we can recruit within 6 months. The intervention will last approximately 12 months (depending on gestational stage at diagnosis – usually this is around 28 weeks but can be earlier), with follow-up stopping at 9 months postpartum. We aim to start recruitment, ethical approval permitting, in March 2018, and finish data collection in September 2019. We expect the data to be analysed by December 2019.

Pregnant women have been chosen because: (1) previous research and our qualitative research indicates this is the best time to recruit women to start providing support, (2) women are already engaged with health services so may be easier to recruit, (3) women may be more receptive to behaviour change support during pregnancy, and (4) the highest cumulative incidence of T2DM after GDM is in the first 5 years postpartum, so any intervention should start as soon as possible after identification of GDM.

Potential participants will be identified by the clinical team working at KCH and GSTT. Potential participants will be given the participant information sheet explaining the purpose of the study. Participants who indicate a potential interest in the study will be given the opportunity to consider their participation in the study before being scanned by the researcher for full eligibility using the eligibility screening form. After screening, if the patient is eligible they will undergo consenting, either on the same day or another day at their convenience. Participants may withdraw their interest in the study at any point during the screening and consenting process and their details will not be stored.

**3.1 Inclusion Criteria**

- aged ≥18 years
- Diagnosed with GDM (NICE criteria)
- ≤30 weeks pregnant
- able to speak and understand English
- Access to the internet
- body mass index (BMI) of ≥ 25kg/m^2^ (or ≥22 kg/m^2^ if Asian)

**3.2 Exclusion Criteria**

- Unable to consent
- Under 18 years
- BMI <24, or <22 in Asian ethnic groups
- ≥31 weeks pregnant
- Unable to speak and understand English
- Serious mental illness
- No access to the internet

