**Figure 1. CONSORT flowchart**

**29-32 weeks' gestation:** Dietician or researcher provide information to potentially eligible participant during group education session. Or clinician providing routine care to approach potentially eligible participants at first clinic appointment - brief verbal and written information given and verbal permission for researcher to contact sought

**Baseline / randomisation visit (29-33 weeks' gestation):** Eligibility confirmed; written informed consent (if not previously obtained); randomisation; demography; questionnaires; anthropometry; blood pressure; blood sample; OGTT, provided with 7 day accelerometer and instructions

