**DECLINED or INELIGIBLE**

Routine demographic data recorded if agreed

**29-33 weeks' gestation:** Eligibility screening, responding to questions about the study and taking informed consent (researcher or clinician conducting routine appointment)

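### Entry is limited to 30 weeks' gestation, but the flowchart approaches women up to 32 weeks and randomises up to 33, and no time point is named for the limit

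*Protocol*

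**What the plan says.** **Eligibility.** Section 3.1 requires "≤30 weeks pregnant", and the synopsis repeats this. Section 3.2 excludes women who are "≥31 weeks pregnant".

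**Procedures.** In the CONSORT flowchart (Figure 1, section 2.3):
- the first approach is at "29-32 weeks' gestation";
- eligibility screening and consent are at "29-33 weeks' gestation";
- the next step is headed "Baseline / randomisation visit (29-33 weeks", and eligibility is confirmed again at that visit;
- the first motivational interviewing session is also at 29-33 weeks.

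The visit table below the flowchart puts the inclusion and exclusion check in the Recruitment column.

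**Forecast.** Section 3 counts about 200 new patients with gestational diabetes a year at one hospital and 700 at the other, and then says: "We estimate that with a 30% recruitment rate we can recruit our sample within 3 months". At a 15% rate it gives 6 months. It places diagnosis usually at around 28 weeks, sometimes earlier.

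**BMI.** Section 3.1 asks for "body mass index (BMI) of ≥ 25kg/m^2" (22 or more if Asian), while section 3.2 excludes "BMI <24, or <22 in Asian ethnic groups".

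**The concern.** Staff who follow the flowchart can approach, consent and randomise a woman at 31, 32 or 33 weeks. Staff who follow sections 3.1 and 3.2 must turn her away. Both instructions are in force, and the protocol does not say whether gestation is judged at diagnosis, first contact, consent or randomisation.

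This matters more here than it would for a minor criterion. The primary outcome is feasibility, and recruitment rate is the first component listed in section 2.4. Two things depend on the rule chosen: whether women at 31-33 weeks belong in the denominator, and whether those randomised count as valid recruits. Recruitment takes place at more than one hospital, so the rule could be applied differently between them. The resulting rate is meant to inform a larger trial.

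**Working it through.** **1. The plan's own forecast.** Inputs are from section 3: 200 and 700 new patients a year, a target of 60, and rates of 30% and 15%.
- Monthly flow: (200 + 700)/12 = 75.
- At 30% over 3 months: 75 × 0.30 × 3 = 67.5.
- At 15% over 6 months: 75 × 0.15 × 6 = 67.5.
- Time to reach 60: 60/(75 × 0.30) = 2.7 months; 60/(75 × 0.15) = 5.3 months.

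The forecast reproduces when every new patient is counted. Its slack is 1 − 60/67.5 = 11%, so it still reaches 60 if about 89% of new patients are eligible.

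**2. How much of each window is outside the criteria.** Each window starts at 29+0 (weeks + days). In completed weeks the limit runs to 30+6, which gives 14 eligible days.

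| Window | Total days | Eligible days | Outside the criteria |
|---|---|---|---|
| Approach, 29-32 weeks | 28 | 14 | 14/28 = 50% (2 of 4 weeks) |
| Screening and randomisation, 29-33 weeks | 35 | 14 | 21/35 = 60% (3 of 5 weeks) |

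The result depends on how the limits are read. The inclusion limit could stop at 30+0 (8 eligible days), and a window could end on the first day of its last week (22 and 29 days in total).
- Approach: lowest 8/22 = 36%, highest 20/28 = 71%.
- Screening and randomisation: lowest 15/29 = 52%, highest 27/35 = 77%.

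More than half of the screening and randomisation window is therefore outside the criteria on every reading. For the approach window the central figure is exactly half.

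**3. What this could mean for the forecast, as an assumption only.** The protocol does not say what share *f* of new patients would be reached within the limit. Time to recruit 60 is 60/(75 × rate × *f*).

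| Assumed *f* | 30% rate | 15% rate |
|---|---|---|
| 1.0 (as forecast) | 2.7 months | 5.3 months |
| 0.8 | 3.3 months | 6.7 months |
| 0.4 | 6.7 months | 13.3 months |

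The table applies only if the 15-30% rate is a share of eligible women. If it is a share of all new patients, ineligibility is already inside it, and multiplying by *f* would count it twice. Section 3 does not say which is meant.

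**The case against.** The best defence is that the limit was meant for first contact only, with later visits allowed to run to 33 weeks. The visit table's placing of the check at recruitment fits that reading. It does not remove the conflict: no section states it, the approach step itself runs to 32 weeks, and eligibility is confirmed again at the randomisation visit.

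That second check, and the flowchart's box for ineligible women, should catch some errors. But the check cannot work consistently while the protocol gives two upper limits.

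A second objection concerns size, and it stands. A reader might infer that losing 3 of 5 weeks means losing 60% of the women, cutting the pool from 75 to 75 × 0.40 = 30 a month. The documents do not support that. Each woman passes through weeks 29 and 30 before reaching 31. Diagnosis is usually around 28 weeks or earlier, and section 3 lets recruitment begin at the diagnosis appointment. Its other routes are alternatives, not successive steps. From 28+0 to 30+6 is 20 days; even after a week's wait for the education session and the 48 hours for reflection in section 4.1, 20 − 7 − 2 = 11 days remain. Women may well cluster in the eligible weeks.

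Nor can one conclude that recruitment would run past the planned end of data collection in September 2019. Even 13.3 months from March 2018 ends around April 2019. An overrun appears only after adding the rest of pregnancy and 9 months postpartum, and it needs the lower rate together with a reduced pool whose size the protocol does not give.

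On BMI, it is tempting to say that non-Asian women at 24.0-24.9 have no defined status. They do: they fail the inclusion criterion and are ineligible. The mismatch is editorial.

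**Conclusion.** The contradiction is explicit and rests on no assumption. The criteria stop at 30 weeks, while the flowchart approaches women to 32 weeks and randomises to 33. In completed weeks, 60% of the screening and randomisation window (52% to 77% over the possible readings) and 50% of the approach window (36% to 71%) lie outside the criteria. Any woman randomised in those later weeks would breach section 3.2, and the recruitment rate has no fixed meaning until one rule is chosen.

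The effect on the number of women and on the timetable cannot be derived from the protocol. The 3.3-6.7 months at 30% and 6.7-13.3 months at 15% rest on an assumed 40-80% of patients falling within the limit, and on the recruitment rate applying to eligible women only. What the figures do show is that the forecast has room for about 11% ineligible and no more.

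**What to change.** Before recruitment starts:

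1. State one upper gestational limit and the time point at which it applies, for example consent or randomisation. Use the same wording in the synopsis, sections 3.1 and 3.2, all the flowchart windows and the eligibility checklist. Say whether the limit is in completed weeks. The sponsor decides whether the limit or the windows move.
2. If the limit stays at 30 weeks, state whether the 15-30% recruitment rate is a share of all 75 new patients a month or of eligible women only. Then re-check the 3- and 6-month forecast on that basis.
3. As a minor edit, align the BMI exclusion cut-off for non-Asian women with the inclusion cut-off.

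The cost is a wording change and a revised checklist. The possible downside is a less favourable recruitment forecast.

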**3.3 Criteria for Premature Withdrawal**

Participants will be free to withdraw from the study at any time without giving reasons and without prejudicing further treatment. If the participant no longer meets the inclusion criteria, for example they are diagnosed with type1 or type 2 diabetes, or they become pregnant they will be withdrawn from the study. Similarly, if the participant is unwell and unable to comply with the other aspects of the protocol or if a participant were no longer able to give informed consent during the study, they would be withdrawn. In all cases where possible and with permission from the participant, any data already collected up until the time of withdrawal would be kept and will be used in the data analysis unless the participant requests otherwise. This will clearly be outlined in the Participant Information Sheet and itemised in the Patient Consent Form.

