**X = all participants**

**X = only participants randomised to intervention group**

**2.4 Outcome Measures**

The primary outcome is feasibility of the trial. This will be assessed during the process evaluation through:

- recruitment rate
- attrition rate
- reasons for non-acceptance
- trial procedures for randomisation
- amount of staff time required
- fidelity, measured through a self-report check-list
- staff feedback on feasibility
- participants’ satisfaction with the intervention
- acceptability of research procedures, data collection and overall experience of the trial

The secondary outcomes will assess preliminary efficacy of the intervention. We will measure the following :

- Oral Glucose Tolerance Test (OGTT) to assess differences ≥1 mmol/l in either fasting or two hour postprandial glucose
- Incident T2DM and a subsequent GDM pregnancy (NICE criteria)
- Relative and absolute weight loss at multiple time points considering the number of women achieving significant weight loss (>5%) at 3 and 9 months postpartum from a baseline of the booking appointment weight
- Lifestyle factors, following the Medical Research Council (2012) diet and physical activity measurement toolkit and from accelerometer
- Other metabolic and anthropometric factors will include HbA1c, waist circumference and blood pressure
- Psychological factors; depression/anxiety (PHQ9) and postnatal depression (Edinburgh postnatal depression scale)
- Health related quality of life- EuroQol EQ-5D-5L will be used to assess health related quality of life
- Diabetes risk perception (Risk Perception Survey for Developing Diabetes used in the DPP [9]).
- Infant factors- infant feeding intentions, breast feeding duration, weight gain and growth, and measure of attachment.
- Attitudes to body [23], eating behaviour [24] and motivation for dietary change [25].
- Additional data will include: age, ethnicity, deprivation, employment, education, pre-pregnancy BMI, parity, previous GDM and birth outcome data

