### 2.4 Trial Statistics and Analysis

We do not yet have the information necessary for a formal power calculation. The aim of this study is to measure feasibility including estimating the effect size and standard deviation to formulate a power calculation for a definitive trial. The sample size of 30 in each arm would be able to detect an effect size of 0.8 in a continuous variable such as weight loss, and if allowing for a 20% attrition rate (n=16), 0.9. Therefore we do not expect do detect differences unless the effect size is large.

For the preliminary efficacy outcomes, between group and group*time interactions will be used to estimate the intervention effects (analysis of variance). The analysis will be performed using SPSS by intention to treat. Further regression analysis will be used to adjust for any potential confounding factors not factored into the stratification.

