### 4. Study procedures

**4.1 Informed Consent Procedures**

Potentially eligible participants attending out-patients diabetes clinics at KCH and GSTT will be given the Patient Information Sheet by the clinician. They will then be given at least 48 hours to consider their participation in the study and discuss the decision with family, friends and their care team. A member of the research team will then contact them by telephone to answer any additional questions, verify their understanding of what is involved and confirm their interest in study participation and to arrange for the screening appointment. If the participant is interested in taking part in the study the researcher will gain written consent and recruit to the study.

For each consent form participants will write their initial next to each statement of the Patient Consent Form and sign next to their name. A suitably trained and experienced member of the research team who is authorised on the Delegation Log will then sign the self-duplicating Patient Consent Form, retain two parts (to be stored securely by the researchers and in the hospital medical notes), and give back one part to be retained by the participant. The right of the participant to refuse to participate without giving reasons will be respected. Recruited participants will be consented prior to any data collection.

All participants are free to withdraw at any time from the study without giving reasons and without prejudicing further treatment. No further data will be collected. Data already collected will still be used in the data analysis unless the participant requests otherwise; this will clearly be outlined in the Participant Information Sheet and itemised in the Patient Consent Form.

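### Section 3.3 ends follow-up at a new pregnancy or a diabetes diagnosis, so the listed subsequent-GDM outcome cannot be observed and 9-month data are lost because of an outcome event

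*Protocol*

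**What the plan says.** Section 3.3 (Criteria for Premature Withdrawal) gives these cases of a woman who has ceased to be eligible: "for example they are diagnosed with type1 or type 2 diabetes, or they become pregnant they will be withdrawn from the study". The wording is withdrawal from the study, not from the intervention sessions. The section adds that, where possible and with permission, "any data already collected up until the time of withdrawal would be kept and will be used in the data analysis unless the participant requests" that they not be used.

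Section 2.4 (Outcome Measures) includes among the secondary outcomes "Incident T2DM and a subsequent GDM pregnancy (NICE criteria"), and also "Oral Glucose Tolerance Test (OGTT) to assess differences ≥1 mmol/l in either fasting or two hour postprandial glucose". Section 4.2 schedules the OGTT, HbA1c, weight and questionnaires at 3 and 9 months postpartum. Section 3 describes the intervention period "with follow-up stopping at 9 months postpartum" and says GDM is usually diagnosed at around 28 weeks, sometimes earlier.

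On analysis, section 2.4 (Trial Statistics and Analysis) says that "between group and group*time interactions will be used to estimate the intervention effects (analysis of variance"). It then names the software and the analysis principle in one sentence: "The analysis will be performed using SPSS by intention to treat". Attrition rate is one of the listed measures of the primary outcome, feasibility.

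No section provides for follow-up, or for finding out about these outcomes, after a withdrawal of this kind.

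**The concern.** The intervention aims to prevent T2DM and further GDM (section 2.2). Under section 3.3, T2DM and the pregnancy that must precede further GDM are events that end a woman's follow-up. This has three consequences.

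- A zero count for subsequent GDM would be produced by the rule and could be misread as a result.
- The 9-month comparison would lack values for women whose glucose was already in the diabetic range at 3 months. The data would be missing because of the outcome. An SAP can say how to handle missing values, but it cannot recover data that the protocol does not collect.
- Withdrawals that the protocol imposes could enter the attrition rate alongside women who chose to leave. That rate is meant to inform the definitive trial.

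**Working it through.** The plan gives no figure to reproduce. The contradiction follows from the order of events, and the arithmetic only shows its scale.

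**1. Subsequent GDM.** The order is pregnancy, then withdrawal (3.3), then GDM diagnosis. The third step always falls after data collection has stopped, so the observable count is 0 in each arm whatever the true rate.

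Without the rule there would still be few events:
- 9 months is about 39.1 weeks.
- Diagnosis at 28 weeks' gestation (section 3) is 28 - 2 = 26 weeks after conception.
- Latest conception is therefore 39.1 - 26 = 13.1 weeks postpartum.
- If diagnosis came at 24 weeks (an assumption), it is 39.1 - 22 = 17.1 weeks.

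**2. Incident T2DM.** The diagnosis that triggers withdrawal is itself the event, so it can be counted once. Section 1.1 gives a risk of 30% within 5 to 16 years. With a constant hazard (an assumption), the 9-month risk is 1 - 0.7^(0.75/T):
- T = 5 years: 5.2%, or 60 × 0.0521 = 3.1 women.
- T = 16 years: 1.7%, or 60 × 0.0166 = 1.0 woman.

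Only those diagnosed before the 9-month visit lose 9-month data, so fewer than this are affected.

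**3. New pregnancies.** The documents give no rate. If 2% to 10% conceive by 9 months (an assumption), that is 60 × 0.02 = 1.2 to 60 × 0.10 = 6 women withdrawn.

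**4. Effect on the 9-month glucose difference.** All inputs here are assumptions, because the protocol gives no glucose mean, SD or correlation. Take 2-hour glucose at 3 and 9 months as bivariate normal with control mean m, common SD s and correlation r, a true 9-month difference of -1.0 mmol/l, and removal at 3 months when the value is 11.1 mmol/l or more.

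In an arm with 3-month mean m3, let a = (11.1 - m3)/s. The fraction removed is 1 - Φ(a), and the 9-month mean of those retained falls by r·s·φ(a)/Φ(a).

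| m, s, r | 3-month effect | Removed, control v intervention | Estimated 9-month difference |
|---|---|---|---|
| 7.5, 2.2, 0.6 | -1.0 | 5.1% v 1.8% | -0.92 |
| 7.5, 2.2, 0.6 | -0.5 | 5.1% v 3.1% | -0.95 |
| 7.5, 2.2, 0.6 | 0 | 5.1% v 5.1% | -1.00 |
| 7.0, 1.8, 0.5 | -1.0 | 1.1% v 0.2% | -0.98 |
| 7.5, 2.2, 0.8 | -1.0 | 5.1% v 1.8% | -0.89 |

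For comparison, with 24 per arm (30 less 20%) and SD 2.2, the standard error of the difference is 2.2 × √(2/24) = 0.64. The largest shift in the table, 0.11, is less than one fifth of that.

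**5. Attrition.** Each 3 imposed withdrawals are 3/60 = 5 percentage points. The plan allows for 20%, which is 12 of 60.

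**The case against.** The strongest reply is that little is lost in practice. This is a feasibility trial. Efficacy is preliminary, and the protocol says differences are not expected to be detected unless the effect is large. Few subsequent GDM diagnoses could fall within 9 months in any case. The case report form has entries for withdrawal (9.2) and the interview asks about reasons for drop-out (4.2), so imposed and voluntary withdrawals could be told apart. These points stand, and they limit the size of the problem. They do not make a listed outcome observable.

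Some stronger readings are tempting but are not supported:

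- **Both outcomes are zero by rule.** Only subsequent GDM is. A first T2DM diagnosis remains countable if it is recorded as the reason for withdrawal.
- **Intention to treat is abandoned.** Section 3.3 keeps and uses earlier data, and no woman is moved out of her randomised arm. The conflict is narrower: follow-up stops because of a post-randomisation outcome event.
- **Section 4.1 bars all later data.** The sentence "No further data will be collected" follows the statement on voluntary withdrawal. It does not clearly govern withdrawals imposed by the protocol, and section 3.3 carries the point without it.
- **The glucose comparison is seriously biased, with unequal loss between arms.** This depends on an effect being present by 3 months. If there is none, removal is equal and the bias is nil.
- **Attrition is inflated beyond 20%.** The protocol does not say whether its 20% includes imposed withdrawals.

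**Conclusion.** The point holds as an internal contradiction between section 3.3 and the two sections numbered 2.4. That subsequent GDM cannot be observed rests on no assumption. The loss of 9-month data for women diagnosed before that visit also follows from the text as written, and it sits badly with the intention-to-treat claim.

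The numerical consequence is modest. About 1 to 3 T2DM cases in 60 are expected under a constant hazard, with possibly a few imposed withdrawals for pregnancy. On assumed inputs, the 9-month glucose difference is shifted by between 0 and about 0.11 mmol/l, towards no effect. The possible mixing of imposed and voluntary withdrawals matters because attrition is a primary measure, but the protocol does not establish that it will happen. The text needs correcting mainly because an analysis plan cannot supply data that were never collected, and because a definitive trial might copy the rule.

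**What to change.** Reconcile section 3.3 with both sections numbered 2.4:

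1. State in 3.3 that a T2DM diagnosis or a new pregnancy is an outcome event and does not by itself end data collection. With the woman's consent, continue the scheduled follow-up data to 9 months, or at least questionnaires and routine-record data.
2. Keep the existing withdrawal provisions for the woman's own request, loss of capacity to consent, and illness that prevents compliance.
3. Report T2DM and new-pregnancy events separately from attrition.
4. Drop subsequent GDM as an outcome, or redefine it as new pregnancy by 9 months.

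Whether intervention sessions or particular tests continue for these women is for the clinical team to decide.

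The cost is wording in the protocol and the information sheet, plus a few follow-up contacts that are already scheduled.

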| Up to first year of life | 1-2 as per early post-partum | 1-3 as per pregnancy +   1. Daily calorie target = 1,200 (+400 if breast feeding). | ≥5% weight loss from 2 months post-partum. |
| *= Cedergren, M. (2007) Optimal gestational weight gain for body mass index categories. Obstet Gynecol. 2007 Oct;110(4):759-64. | | | |

The intervention is comprised of 5 face to face interactions (60 minutes) across the antenatal and postpartum periods delivered using motivational interviewing (MI) techniques. The focus of the sessions are targeted to reflect the changing context of needs during pregnancy and the postpartum period. The intervention is supported by a facilitated ‘WhatsApp’ group, motivational text messages, a pedometer and a website. An overview of the GODDESS intervention is provided in figure 1.

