**Face-face MI session 4 (6 months postpartum)**

**Face-face MI session 3 (3 months postpartum)**

**DROP OUT**

Pre-collected data used if agreed

**Interim data visit (3 months postpartum):** Questionnaires; anthropometry; blood pressure; blood sample; OGTT; provided with 7 day accelerometer

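### Section 3.3 does not separate stopping the intervention from leaving follow-up, so illness can end outcome collection despite the intention-to-treat analysis

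*Protocol*

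**What the plan says.** Section 3.3 first covers women who no longer meet the inclusion criteria, for example through a diabetes diagnosis or a new pregnancy: "they become pregnant they will be withdrawn from the study". The next sentence extends the same consequence, by the word *similarly*, to illness: "if the participant is unwell and unable to comply with the other aspects of the protocol". For all such cases the section then says that "any data already collected up until the time of withdrawal would be kept and will be used in the data analysis unless the participant requests" that it be left out. The flowchart in section 2.3 has a single drop-out box, which reads "Pre-collected data used if agreed". The case report form contents in section 9.2 list study withdrawal and have no entry for stopping the intervention alone.

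Section 4.1, in its paragraph on a participant's own decision to withdraw, adds "No further data will be collected".

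The statistics section states: "The analysis will be performed using SPSS by intention to treat". Section 2.4 (Outcome Measures) puts the attrition rate among the primary feasibility measures, and PHQ-9, EPDS and EQ-5D-5L among the secondary outcomes. Section 4.2 schedules these three instruments at baseline and at 3 and 9 months postpartum in both arms.

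On what there is to comply with, section 2.2 says: "The intervention is comprised of 5 face to face interactions (60 minutes) across the antenatal and postpartum periods", supported by a WhatsApp group, text messages, a pedometer and a website. The control arm has routine care and the same data visits.

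**The concern.** Intention to treat needs outcomes on women as randomised, whether or not they keep up with the programme. Section 3.3 offers only one exit. A woman who is ill and cannot keep up leaves the study, and her outcome record ends there, even if she could still have filled in questionnaires or allowed her routine records to be used. The investigator imposes this; she does not request it.

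Two things are at stake. First, the reason for the missing values is health, and three of the outcomes lost measure health, so the missingness may be informative. If it also differs between arms, it biases the comparison that is meant to supply an effect size for the definitive trial. Second, the attrition rate combines women who could not continue the programme with women from whom data could not be obtained. A definitive trial must plan for those two quantities separately.

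**Working it through.** **Does the rule end follow-up?** Reading the sections together:

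- Section 3.3: illness plus inability to comply leads to withdrawal from the study, and only earlier data are kept.
- Section 2.3, drop-out box: the same, earlier data only.
- Section 4.1: nothing further is collected, but this is written for voluntary withdrawal. The conclusion therefore rests on 3.3 and the flowchart.
- Section 4.2: the 9-month interview covers reasons for dropping out. It is qualitative and lists none of PHQ-9, EPDS or EQ-5D-5L.

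A woman withdrawn before 3 months postpartum thus has no postpartum values. One withdrawn between the two visits has 3-month values only.

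**Attrition.** The protocol gives no withdrawal rate for illness, overall or by arm. Its only related figure is the 20% attrition allowance in the statistics section, which is not divided by reason. With 30 per arm, 0.20 × 30 = 6 per arm. If 3 of 30 women in an arm (10%, assumed) were withdrawn under this clause, they would use 3/6 = half of that arm's allowance without any of them having declined data collection.

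**Possible bias (illustration; all rates assumed).** Take a standardised outcome with no true treatment effect. Each arm loses the worst-off fraction *f* on an illness scale that correlates ρ with the outcome. The mean of those remaining shifts by

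ρ × φ(c) / (1 − f), with c = Φ⁻¹(1 − f).

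At ρ = 1:

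- f = 3.3% (1 of 30): 0.077 SD
- f = 10% (3 of 30): c = 1.282, φ(c) = 0.1755, and 0.1755 / 0.9 = 0.195 SD
- f = 20% (6 of 30): c = 0.842, φ(c) = 0.280, and 0.280 / 0.8 = 0.350 SD

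The spurious difference in favour of the intervention is the gap between the two arms' shifts, multiplied by ρ:

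| Loss, intervention v control | ρ = 1 | ρ = 0.5 | ρ = 0.25 |
| --- | --- | --- | --- |
| 10% v 0% | 0.20 | 0.10 | 0.05 |
| 20% v 0% | 0.35 | 0.17 | 0.09 |
| 10% v 3.3% | 0.12 | 0.06 | 0.03 |
| 10% v 10% | 0 | 0 | 0 |

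A cruder model gives similar sizes. If the women removed from one arm score 1.5 SD worse than the rest (assumed), the shift is the proportion removed × 1.5: 0.05 × 1.5 = 0.075, 0.10 × 1.5 = 0.15 and 0.20 × 1.5 = 0.30 SD.

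For scale, the standard error of a 30 v 30 difference is √(2/30) = 0.26 SD.

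**The case against.** The clause names no arm, session or device. It requires illness as well as inability to comply, so missing sessions alone does not trigger it. A reader might infer that an unwell woman is withdrawn in the intervention arm and kept in the control arm. The wording does not say so, and a control woman too ill for the data visits meets the same clause.

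The difference in burden is also smaller than five sessions against none suggests. Sessions 1, 3 and 5 fall at the data-collection time points, leaving sessions 2 and 4 as separate contacts. The data visits are demanding in both arms. Withdrawal at session 5 costs little, because the last data visit is due at the same time.

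The bias figures follow from assumed losses. Most of them lie below the standard error, and they concern secondary outcomes for which the protocol itself expects to detect only large effects. How missing data are analysed is normally left to the statistical analysis plan.

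All of this stands as a limit on how far the point goes. It does not answer the central point, because whether outcomes are collected at all after a woman stops the intervention is settled by the protocol. An analysis plan cannot recover values that were never sought.

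**Conclusion.** The point holds in limited form. The protocol treats being ill and unable to comply as leaving the study, provides no way to stop the intervention and stay in follow-up, and so works against its own intention-to-treat statement. Later depression and quality-of-life values may be informatively missing, and the attrition rate mixes two kinds of loss.

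Three stronger readings are not supported:

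- **Loss does fall more on the intervention arm.** This is plausible because that arm has more to comply with, but no rate by arm is given and the bias is zero if loss is equal.
- **The analysis becomes per-protocol.** Earlier data from withdrawn women are kept and analysed, and nothing excludes women for poor adherence. The problem is missing outcomes.
- **The women lost are those with postnatal depression.** The protocol does not define *unwell*, and it may be physical.

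The size is unknown from the protocol. Under the assumed losses above it runs from zero to 0.35 SD, with 0.03 to 0.12 SD where loss is 10% against 3.3%. This is a low-cost improvement worth making and does not invalidate the design.

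**What to change.** Reconcile section 3.3 with section 4.1 and the intention-to-treat statement by defining two events:

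1. Stopping some or all intervention components. The woman stays in the study and, if willing and able, is still invited to the 3- and 9-month data collection, either in full or as questionnaires and routine records only.
2. Withdrawal from the study and its data collection.

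Record the two separately in the case report form, mirror them in the flowchart, report both by arm, and analyse all women as randomised.

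The cost is amendment wording and one case report form field. The downside is some partial data and a few more follow-up contacts. The change concerns data collection only: it proposes no clinical stopping rule for unwell women, leaves voluntary withdrawal as it is, and does not touch the diabetes and new-pregnancy criteria in 3.3, which are outside this point.
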